### Participant flow

#### Participant identification

PRIME aimed to detect all people with schizophrenia in Sodo by training key informants (HEWs and community leaders) to identify possible cases. This method was successful at identifying people with psychosis in previous Ethiopian studies, including in the neighbouring district [41, 49, 50]. Possible cases of schizophrenia were invited to their health centre for diagnosis and treatment. If they attended, a psychiatric nurse conducted a diagnostic interview using the OPCRIT (Operational Criteria for Research), an operational criteria checklist for psychotic and affective illness [51, 52]. The OPCRIT facilitated the nurse to determine if participants had a DSM-IV diagnosis. Substantial inter-rater reliability and convergent validity of the OPCRIT has been demonstrated in other settings [53] and there is good experience of using OPCRIT in a clinical trial of schizophrenia in the neighbouring district [54]. All confirmed cases of schizophrenia spectrum disorders were offered FBC and, where they consented, were recruited into the PRIME cohort. Prior to RISE recruitment a psychiatrist conducted an additional paper-based diagnosis review of all PRIME cohort participants using the clinical instruments completed at baseline, including the OPCRIT. Where the psychiatrist deemed the diagnosis unclear, a repeat clinical assessment by the psychiatric nurse will be completed prior to RISE recruitment.

### Participant recruitment

Participants for the RISE trial will be primarily recruited from people who were identified and received a diagnosis of a schizophrenia spectrum disorder at the baseline of the PRIME cohort and their caregivers, and were living in the sub-districts selected to participate in the RISE trial. However, we will recruit from up to four pools of potential participants, known as recruitment levels.

*Level 1 recruitment* comprises recruitment from the PRIME cohort at the 6-month data collection interview, which takes place at the health centre. *Level 2 recruitment* comprises recruitment from PRIME cohort drop-outs, i.e. those who do not attend the PRIME 6-month data collection. *Level 3 recruitment* comprises recruitment from those who were identified by key informants but have never attended FBC. This group had some baseline data collected through a home visit by PRIME as part of a non-engagement study. *Level 4 recruitment* comprises recruitment from those individuals who were identified by key informants as potential cases with schizophrenia *after* the recruitment for the PRIME cohort had ended. Level 1 recruitment will take place at consecutive pairs of health centre catchment areas, determined by the PRIME data collection schedule. For levels 2, 3 and 4 recruitment, all sub-districts will be covered equally to avoid unequal recruitment by treatment arm. RISE recruitment will take place either at the health centre at PRIME data collection or at a follow-up visit at the participant’s home.

The aim of incorporating non-PRIME cohort participants is that these non-engagers in care are likely to have more complex needs, and be more symptomatic and disabled. They are, therefore, the individuals who are likely to receive the most benefit from CBR. Some of these individuals will not be accessing care because they are currently well, and will be excluded from the trial using the standard recruitment criteria.

Within each CBR worker area, the transition from one recruitment level to the next will continue until approximately eight participants have been recruited for each CBR worker. The aim is to ensure CBR workers have equal workloads, to ensure CBR delivery is as uniform as possible. If it is not possible to recruit eight participants in any particular CBR worker area (after exhausting all recruitment levels), recruitment will continue at other CBR worker areas whilst aiming to keep the number of participants per CBR worker as equal as possible. Recruitment will proceed to the next recruitment level/s until a maximum of 12 participants per CBR worker are recruited. This is because the maximum feasible workload for CBR workers is expected to be 12 participants. There may be slight adjustments to the number of participants recruited per CBR worker depending on drop-out of CBR workers or other unforeseen factors.

### Recruitment procedures

The recruitment procedures for each of these groups will be detailed in dedicated Standard Operating Procedures (SOPs). Potential participants in the PRIME cohort will have their eligibility for the RISE trial checked by the trial coordinator or trial nurse using PRIME 6-month data (i.e. WHODAS 2.0, BPRS-E, CGI, LIFE chart and LCS). Eligible participants will be invited to join the RISE trial by a trial nurse. They will be given information about the trial in a way appropriate to the participants’ literacy level, which may include verbal information. The trial nurse will then conduct the consent procedures.

Participants not in the PRIME cohort will have an initial consent taken, before data is collected on the eligibility instruments, including the diagnostic interview. Those who are eligible will then be consented to take part in the RISE trial. Those who consent (or, for those without decision-making capacity, whose caregiver consents on their behalf) will complete the full RISE baseline data collection.

### Allocation

The randomisation of sub-districts to intervention and control arms will take place before recruitment. The rationale is that it is necessary to commence delivery of the CBR intervention immediately after recruitment. The trial coordinator will keep the sub-district allocation list secure on a password-protected document. To reduce selection bias, the potential participant will not be informed of the allocation of their sub-district until after they have consented to participate and all baseline data collection is complete. The trial nurse will also be blind to the allocation. The trial coordinator will assign a unique trial identifier (ID) to each new participant and will determine the allocation of all new recruits using the secure allocation list. Recruitment and participant flow will be closely monitored by the trial coordinator and any protocol deviations recorded and reported.

### Outcome assessments

#### Quantitative

All outcomes are individual-level and will be assessed at 6 and 12 months (Table 3). Baseline RISE data will be extracted from 6-month PRIME cohort data and 6-month RISE data will be extracted from 12-month PRIME cohort data. Twelve-month RISE data will be collected independently of the PRIME cohort. Trained lay data collectors will collect all data except for symptom severity, clinical course, overall clinical impression of illness severity and improvement, and medication, for which a trained psychiatric nurse will be used. Patient outcomes will be collected with the caregiver present according to participant preference and when the patient does not have the capacity to answer questions independently. Data will be collected directly from the patient where possible (except for caregiver-reported outcomes). Items will be recorded as missing in the scenario that the caregiver is not present due to patient refusal, and the patient is unable or unwilling to respond. Quality will be assured through systematic observations of data collection by a research assistant (for lay data collectors) or psychiatrist (for psychiatric nurse data collectors), and by verification of all patient record forms. Regular meetings will be held to provide feedback to data collectors.

**Table 3 Tab3:** Summary of outcome measures

Outcome	Instrument
Psychiatric nurse-administered interview with patient	
Symptom severity	Brief Psychiatric Rating Scale – Expanded version (BPRS- E) [62]. A 24-item instrument focussing on psychotic symptoms, but also covering somatic concerns, anxiety, depression and mania. Individual BPRS-E items and total score are sensitive to change in persons with persistent schizophrenia [63]. The scale has been previously used in Ethiopia [64] and has recently been shown to have good inter-rater reliability (>0.8 comparing psychiatric nurses and psychiatrists) in this setting (personal communication, [name]) [65]. As the scale is clinician-rated this allows for sociocultural sensitivity. Inter-rater and test-retest reliability as well as internal consistency are also high in high-income settings [66]
Clinical impression	Clinical Global Impression (CGI). A widely used assessment tool, comprising three scales, to determine overall illness severity and efficacy of intervention [67]
Relapse	Life Chart Schedule (LCS) including course type and relapses [68].
	Longitudinal Interval Follow-up Evaluation: DSM-IV version (LIFE). A semi-structured interview to determine the subject’s psychiatric course since the last interview [69]. Satisfactory validation has been conducted in Ethiopia and the reliability data is currently being analysed. Any necessary adjustments will be made on the basis of the inter-rater reliability assessments (personal communication, [name])
Lay data collector-administered interview with the patient	
Disability	Patient-reported 36-item WHODAS (Disability Assessment Schedule) 2.0 [55].
	A validated indigenous functioning scale, specific to the Ethiopian context [70]
Economic activity	Measure covering current employment, subsistence farming work, income, and hunger due to lack of resources
Discrimination	Section 1 of the Discrimination and Stigma Scale-12 (DISC-12) [71]
Medication adherence	Adapted Morisky Medication Adherence Scale (MMAS) [72]. This scale has previously been utilised for antipsychotic medication adherence [31, 73]. Good construct validity has been demonstrated in Ethiopia (personal communication, [name]) [65]).
	A 5-point nominal scale measuring frequency of adherence [31]
Health service use and costs including engagement with FBC for schizophrenia and physical health conditions	An adapted version of The Client Service Receipt Inventory (CSRI) will enquire systematically about the costs (direct and indirect) of help-seeking from biomedical, traditional and religious healers [74, 75]. The CSRI has been translated into Amharic and found to be acceptable and feasible [76]
Access to community interventions (including CBR components)	Including person administering the component, and satisfaction
Physical restraint	In the preceding 1 and 6 months. Includes assessment of duration, perpetrator, setting and reason for restraint
Nutritional status	Measurement of weight (kg) and height (m) will be carried out [77] and body mass index (weight in kg/(height in m)^2^) calculated
Depression	The Patient Health Questionnaire- 9 (PHQ-9). A 9-item scale which scores each of the 9 DSM-IV criteria for depressive disorders as ‘0’ (not at all) to ‘3’ (nearly every day) [78]. Shown to be valid in the Ethiopian setting [79]
Alcohol use disorder	The AUDIT (Alcohol Use Disorders Identification Test) is a ten-item tool to detect hazardous drinking [80]
Social support	Oslo-3 Social Support Scale [81]
Serious adverse events	Occurrence of serious adverse events (for example, suicide attempt and hospitalisation for medical emergency) in the last 6 months
Lay data collector interview with the primary caregiver	
Patient disability	The 36-item WHODAS 2.0 proxy version will assess functional impairment from the caregiver’s perspective [82, 83]
Economic activity of caregiver	Employment, subsistence farming work, income, and hunger due to lack of resources
Caregiver burden	The Burden Section of the WHO ‘Family Interview Schedule’. This scale, covering financial strain and work difficulties has been previously used in Ethiopia for persons with schizophrenia [2].
	A scale developed for PRIME will quantify the time burden of caring for their relative with schizophrenia, the type of work that was stopped or reduced and the amount of money lost. The Involvement Engagement Questionnaire (IEQ) will be used as an additional measure to assess caregiver burden.
Caregiver depression	PHQ-9 [78, 79]
Stigma	Section of the WHO ‘Family Interview Schedule’; previously used in Ethiopia [8]
Patient medication adherence	The 5-point nominal scale developed for the COPSI study will be used [31]

*CBR* community-based rehabilitation, *DSM-IV Diagnostic and Statistical Manual of Mental disorders, version four*, *FBC* facility-based care

In order to reduce information bias data collectors will be masked to sub-district allocation; participants will be requested not to divulge treatment allocation to data collectors; participants from different sub-districts will be allocated to each data collector; identical methods for follow-up will be employed in each arm; and those involved in data analysis will be masked to sub-district allocation.

Loss to follow-up will be minimised by reminding participants to attend the interview shortly before they are due, either by telephone or by a home visit. Participants who do not attend will receive a home visit to ask them to attend at an alternative time. Data collection will take place at the health centre except for participants who do not attend after three invitations. These participants will receive a home visit for data collection. Participants will receive a modest fee for transport and time compensation.

The primary outcome is proxy report of patient disability which will be measured with the 36-item WHO DAS (Disability Assessment Schedule) 2.0 [55], through interviewing the caregiver. WHODAS 2.0 was developed as single generic instrument for assessing health status and disability relating to a range of health conditions across cultures and settings. It covers understanding and communication, getting around, self-care, getting along with people, life activities and participation in society. Sociocultural adaptation and validation (convergent validity, construct validity and responsiveness to change) of the WHODAS 2.0 in persons with schizophrenia has been completed in Ethiopia (personal communication, [name]). Issues arising during the adaptation included items not having obvious direct translations and representing uncommon experiences in the rural Ethiopian setting (for example, ‘staying by yourself for a few days’). These issues were largely resolved through iterative adjustments to the translation following piloting. The proxy WHODAS 2.0 interview is designed to be answered by a friend, relative or carer. The rationale for using the proxy version for the primary outcome is that this may give a more valid picture of disability level. A separate study in the neighbouring district found that whilst scores from patient- and proxy-reported versions are moderately correlated, there is a difference, with the caregiver scores tending to be higher (greater disability) (personal communication, [name]). Patients may not have enough insight to answer accurately and, therefore, underreport disability. They may also be too unwell to answer all questions, increasing the amount of missing data. Table 3 lists the secondary outcomes, which include patient-reported WHODAS 2.0, symptom severity, relapse, medication adherence, economic activity in the patient and caregiver, discrimination, health service use and costs, physical restraint, nutritional status, caregiver burden, caregiver depression and caregiver stigma. All instruments have been adapted for use in Ethiopia; further details on validation and reliability are also given in Table 3.

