## Background

Schizophrenia can be a severe, chronic and disabling condition, which places a high social and economic burden on individuals [1], families [2] and society. The majority of people with schizophrenia in sub-Saharan Africa do not have access to adequate care [3]. Over half of the people with schizophrenia in Ethiopia experience continuous or episodic illness over a 10-year period [4], where the treatment gap is estimated to be 90 % [5, 6]. Mortality is high; the standardised mortality ratio for people with schizophrenia in Ethiopia is twice that of the general population [7]. People with schizophrenia are also likely to experience stigma and discrimination [8, 9] and human rights violations [10].

According to global consensus, supported by scientific review of the evidence and the experience of mental health system experts, a comprehensive mental health system includes both community- and hospital-based components of care [11, 12] and should incorporate both medication and psychosocial interventions [13, 14]. Relatively low-intensity psychosocial community-based programmes, which are likely to be most feasible, have been shown to be effective in low- and middle-income country (LMIC) settings [15–17]. To date such programmes have typically involved four groups: the patient, family members, a community-based non-specialist key worker and a psychiatrist [14]. In particular, the World Health Organisation’s (WHO’s) mental health Gap Action Programme (mhGAP) recommends community-based rehabilitation (CBR) as an adjunct to medication for schizophrenia [18]. CBR is a general approach with the aim to improve the quality of life and social inclusion of people with disabilities [19] and is typically delivered by trained lay workers from the local community. Key pillars of a CBR programme include interventions that promote health, education, livelihood, and social life. In addition there is a cross-cutting emphasis on empowerment, such as supporting people with disabilities to make their own decisions. CBR is put into practice through the joint endeavours of people with disabilities, their caregivers, community members and relevant governmental and non-governmental services, including health services [20].

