### Power calculation

We estimate that 182 participant dyads (mean 3.4 participants/sub-district) will be available for recruitment. Assuming that there is 23 % attrition, the final sample size for analysis will be 140 participant dyads in 54 sub-districts (mean 2.6 participants/sub-district). This sample size will allow us to detect a 20 % absolute difference in WHODAS 2.0 scores between treatment arms with 85 % power and 5 % significance, assuming a *k* (coefficient of variation) of 0.14 and a within-cluster standard deviation (SD) of 16. The value of *k* was extracted from symptom severity data by sub-district from an RCT in Butajira evaluating trimethoprim as an adjuvant treatment for schizophrenia (*k* = 0.11) [57]. A more conservative estimate of *k* has been used to account for the potential therapist effect; each CBR worker will cover around three sub-districts and CBR intensity and quality may differ by CBR worker. The mean WHODAS 2.0 in intervention and control arms and within-cluster SD were derived from an Indian study of people with schizophrenia [58].

The estimate of 182 participant dyads available for recruitment was arrived at using (1) the total adult population of Sodo district, (2) the local prevalence of schizophrenia (0.05 %) [59], (3) an estimate that 60 % of cases will be detected and agree to participate in the PRIME cohort, (4) an assumption that 70 % of cases will be eligible for RISE, based rates of continuous illness found in a previous study in the neighbouring district of Butajira [5], and (5) an assumption that approximately 80 % of eligible cases will agree to participate, based on previous recruitment rates in the Butajira cohort study [5].

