### Trial management and monitoring

The trial is sponsored by the London School of Hygiene and Tropical Medicine. A Data Safety and Monitoring Board (DSMB) has been convened to assure the continuing safety of research participants. A clinical monitor will carry out onsite monitoring visits prior to the trial commencing, at recruitment, and at 6-month and 12-month follow-up. The trial coordinator will carry out day-to-day monitoring and will also review recruitment rates, withdrawals and losses to follow-up. All protocol violations will be recorded and included in reports of trial findings.

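### The one serious adverse event item the article describes is put to the patient with a fixed 6-month look-back, so it cannot record a death or reach months 0–6 after a missed 6-month interview

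*Protocol article*

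**What the plan says.** Table 3 (Outcome assessments, Quantitative) groups the measures by who is interviewed and by whom. Serious adverse events are the last row of the block headed "Lay data collector-administered interview with the patient". The row reads "Occurrence of serious adverse events (for example, suicide attempt and hospitalisation for medical emergency) in the last 6 months". The caregiver block that follows has no such row, although it does ask the caregiver about the patient's disability and medication adherence. Death appears neither as an example of a serious adverse event nor as an outcome.

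On timing, the same section states: "All outcomes are individual-level and will be assessed at 6 and 12 months (Table 3").

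On the respondent, it states "Patient outcomes will be collected with the caregiver present according to participant preference and when the patient does not have the capacity to answer questions" without help. It adds "Items will be recorded as missing in the scenario that the caregiver is not present due to patient refusal, and the patient is unable or" (the sentence closes by including a patient who declines to answer).

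Non-attenders are followed up with reminders and, after three invitations, a home visit for data collection. Follow-up methods are to be identical in each arm. Under Trial management and monitoring, a DSMB "has been convened to assure the continuing safety of research participants", a clinical monitor makes onsite visits, and the trial coordinator reviews withdrawals and losses.

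**The concern.** The item has two features that work against it: who is asked, and over what period.

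A patient interview can only be answered by a living patient who is reached and able to respond. Suicide attempts, emergency admissions and deaths can themselves be reasons why a patient is not interviewed, so the item is weakest where events are most likely. The Background section stresses that mortality is high: "the standardised mortality ratio for people with schizophrenia in Ethiopia is twice that of the general population".

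A fixed 6-month look-back covers the trial year only if both interviews take place. A patient who misses the first and attends the second is never asked about the first half-year.

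At stake is whether the serious adverse event outcome by arm is complete. The document's primary analysis and sample size are not affected.

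**Working it through.** **Inputs.** From Power calculation: 182 dyads recruited, 23 % attrition, and "the final sample size for analysis will be 140 participant dyads in 54 sub-districts". From Table 3: respondent is the patient; window is 6 months. From Outcome assessments: interviews at 6 and 12 months. The article gives no serious adverse event rate and no absolute death rate.

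**Step 1. Reproduce the plan's own figure.** 182 × (1 − 0.23) = 140.1, which agrees with the stated 140. In reverse, 140 / 0.77 = 181.8, which agrees with 182. The planned loss is 182 − 140 = 42 dyads, and 42 / 182 = 23.1 %.

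**Step 2. What the fixed window covers.**

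| Interviews completed | Months asked about | Months not asked about |
|---|---|---|
| 6 and 12 | 0–12 | none |
| 6 only | 0–6 | 6–12 |
| 12 only | 6–12 | 0–6 |
| neither | none | 0–12 |

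A death is outside the item in every row, because the respondent is the patient. A look-back running from the last completed interview or enrolment would close the gap in the third row. The second and fourth rows need another source.

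**Step 3. Size on the planning assumption.** Count a full year for each of 182 patients, i.e. 182 person-years, and suppose 42 give no 12-month report.
- If all 42 were interviewed at 6 months: 42 × 0.5 = 21 person-years not asked about; 21 / 182 = 11.5 %.
- If none of the 42 was: 42 × 1 = 42 person-years; 42 / 182 = 23.1 %.

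Each patient who misses only the 6-month interview adds another half person-year. The article gives no figure for that group.

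**Step 4. Compare with the article's own choices.**
- *Respondent.* The article takes the primary outcome from the caregiver because patients may lack the insight to answer accurately or be too unwell to answer every question. The same reasons apply to reporting a suicide attempt or an emergency admission, yet that item stays with the patient, although the caregiver is interviewed anyway.
- *Window.* In the same table, LIFE asks about psychiatric course from the previous interview onwards. The serious adverse event row uses a fixed period instead.

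**The case against.** The strongest reply is that Table 3 summarises outcome measures and is not a safety-reporting procedure. The article condenses a fuller protocol that is not shown. It mentions a DSMB, a clinical monitor, coordinator review of losses, and data collection under GCP and SOPs. A reader might infer from the table that serious adverse events are collected only by this interview, that deaths and events in people who leave go uncounted, or that the DSMB sees an undercount. The documents support none of these. Nothing says the interview is the sole route, and nothing says where the DSMB's data come from. Notification of deaths and expedited reporting are commonly left to the full protocol, so their absence here is no finding.

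Four further points hold in part.
- *Home visits.* They make a missed interview less likely, so the months 0–6 gap arises only when they fail at 6 months and the patient is then seen at 12. They do not alter the window, and they cannot make a patient interview record a death.
- *Caregiver presence.* The caregiver may sit in, and an item is set to missing only when the patient has refused the caregiver's presence and also cannot or will not respond. Unwellness alone does not trigger the rule. Caregiver input still depends on a patient interview taking place.
- *Overlapping instruments.* LIFE, the Life Chart Schedule and the service-use inventory will pick up some relapses and admissions. They are not a serious adverse event record.
- *Size.* The 23 % is a planning figure for dyads in an analysis whose primary outcome is caregiver-reported. It is not a forecast of missing patient reports. Any count of deaths would need a mortality rate that the article does not give.

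Differential loss by arm is likewise not shown; the article plans the same follow-up in both arms.

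**Conclusion.** The point stands as a criticism of the item that Table 3 fixes, not of the trial's whole safety system. The only serious adverse event ascertainment the article describes is asked of the patient, uses a fixed 6-month window, omits death and has no caregiver counterpart. That sits badly with the article's own reasons for preferring the caregiver on disability and with the look-back it uses for LIFE.

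On the 23 % planning assumption, up to about 42 of 182 dyads would give no 12-month report. That corresponds to 21 to 42 of 182 person-years (about 12 % to 23 %) not asked about, depending on attendance at 6 months. These figures treat planned dyad attrition as a stand-in for missing patient interviews. The number of deaths cannot be derived, because the article gives a mortality ratio and no rate. No sample-size or power figure changes. The improvement is cheap and should be made.

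**What to change.** 1. In Table 3, add the serious adverse event item, including death with date and cause, to the primary caregiver interview at 6 and 12 months.
2. For patient and caregiver alike, replace the fixed 6 months with the time since the last completed RISE interview, or since enrolment if there has been none.
3. For dyads not interviewed, record vital status and serious adverse events at the home visits already planned for non-attenders, in the same way in both arms. An identical source matters because only the intervention arm has regular CBR visits and logbooks through which events might come to notice informally.
4. Report events by arm for all enrolled participants, with the number in each arm for whom the period is not covered.

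Cost: one more item on a form already in use, a changed look-back phrase, a few extra minutes per interview, and longer recall for those who missed a visit. If the full protocol already names a source for deaths and for events in non-interviewed participants, a sentence in the article pointing to it would meet part of item 3; the respondent and window in Table 3 would still merit the change.
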